## Abstract

**Background:**

Adequate bowel preparation is required for magnetic resonance enterography (MRE), which can be achieved by administering contrast solution after mid-gut tubing or taking contrast solution orally. We present the design of randomized controlled trial (RCT) to compare the efficacy and compliance of bowel preparation between mid-gut tubing and oral administering for MRE in patients with Crohn’s disease (CD).

**Methods/design:**

This is an open-label, multicenter RCT. Ninety-six patients with CD in need of MRE examination and mid-gut tubing (prepared for fecal microbiota transplantation and/or enteral nutrition), aged ≥ 14 years, will be included. Patients will be randomized 1:1 into either bowel preparation by oral administering (oral group) or bowel preparation through mid-gut transendoscopic enteral tubing (TET) (tubing group). The primary outcome measures are: (1) degree of discomfort before/during/after bowel preparation for MRE using a visual 5-grade scale (1 = few, 5 = very severe); and (2) grade of bowel distention evaluated by a 5-grade scale (1 = 0–20% segmental distention, 2 = 20–40% distention, 3 = 40–60% distention, 4 = 60–80% distention, 5 = 80–100% distention). The secondary outcome measure is the accuracy of lesion detection through MRE confirmed by colonoscopy which is evaluated by a 5-point scale.

**Discussion:**

The outcome of this study is expected to provide a novel effective clinical protocol of bowel preparation for MRE in patients with CD. We hope to highlight the concept of physician–patient satisfaction based on different methods of bowel preparation for MRE.

**Trial registration:**

ClinicalTrials.gov, NCT03541733. Registered on 30 May 2018.

**Electronic supplementary material:**

The online version of this article (10.1186/s13063-018-3101-x) contains supplementary material, which is available to authorized users.

## Background

Crohn’s disease (CD) is a chronic inflammatory disorder that may invade the gastrointestinal tract from mouth to anus; it is characterized by periods of flare-up with active symptomatic disease and periods of remission [1]. Inflammation of CD is transmural and therefore may be complicated by fistula, abscess formation, perforations, and fibrotic strictures. The frequent and periodic evaluations of inflammation of CD are vital in planning a proper therapy, monitoring the drug effects, and detecting recurrence [2].

Magnetic resonance enterography (MRE), a target examination of the gastrointestinal tract, has been shown to be highly effective in the diagnosis and management of patients with CD [3]. A recent systematic review indicated that the sensitivity and specificity of MRE for the diagnosis of suspected CD were 78% and 85%, respectively [4]. For the extension of CD lesions, the sensitivity and specificity of MRE for small bowel lesions were 74% and 91%, respectively [4]. On a per-patient basis, MRE had an overall sensitivity of 91% and a specificity of 71% for active disease [5]. Compared with other imaging examinations, MRE has many advantages such as no ionizing radiation, offering better soft tissue contrast resolution, superior evaluation of perianal disease, better distinction between acute and chronic disease, distinguishing from prominent muscle hypertrophy to prominent fibrosis [6], and superior detection of fistulas and strictures in CD with functional techniques such as diffusion-weighted magnetic resonance imaging (DW-MRI) and dynamic contrast-enhanced MRI (DCE-MRI) [7].

MRE examination requires adequate bowel distention as collapsed loops may hide lesions or mimic disease by suggesting a thickened bowel wall [8]. Bowel distention can be achieved by two methods, administering contrast solution after mid-gut tubing and administering contrast solution orally. Mid-gut tubing, such as nasojejunal tubing and nasoduodenal tubing, provides better bowel distention [9, 10]. Traditionally, mid-gut tubing can be operated under fluoroscopic or electromagnetic guidance or with endoscopic assistance. The procedure of conventional tubing is considered to be unpleasant and time-consuming, and/or with radiation in patients especially younger ones [10]. The transendoscopic enteral tubing (TET) in mid-gut is a novel and quick technique of enteral tubing under the endoscopy [11]. The mean procedure time (from the beginning of inserting the tube into the esophagus to the tube being fixed on the pylorus wall by one titanium clip) for tubing was 4.2 ± 1.9 min (range, 1.53–11.25 min) [11]. The mid-gut tube can be used for repeat fecal microbiota transplantations (FMTs) and enteral nutrition support in CD [12–14]. Furthermore, based on our practice, we found that the mid-gut tube might be used as a perfect delivering for the large volume laxative and contrast solution for bowel preparation for MRE. Bowel preparation for MRE includes bowel cleaning and bowel distention. Administering solution through the mid-gut tube may lead to better bowel distention and alleviates adverse symptoms from drinking a large volume of fluid laxative and contrast solution. In clinical practice, some patients may not tolerate a large oral fluid load, leading to adverse symptoms such as nausea, vomiting, bloating, abdominal pain, and diarrhea [15–17]. In addition, despite large oral volumes, distention of the distal small bowel, where diseases are most likely to occur, can still be poor [5]. This not only aggravates the mental pressure of patients, but also affects the accuracy of the judgment from the physicians for the disease. Therefore, our study aims to evaluate the efficacy and compliance of bowel preparation through mid-gut tubing for MRE in patients with CD.

## Methods/design

This study is conducted in China as an open-label, multicenter RCT with a parallel group design. Flow chart of the trial is shown in Fig. 1. The procedure and checklist of this trial are shown in SPIRIT figure (Fig. 2) and Additional file 1: SPIRIT checklist, respectively.

**Fig. 1 Fig1:**
[figure not shown]
*Flow chart* of the trial

**Fig. 2 Fig2:**
[figure not shown]
SPIRIT figure

### Participants

Participants will be recruited to the study from the gastroenterology inpatients at the Second Affiliated Hospital of Nanjing Medical University, Sir Run Run Shaw Hospital at Nanjing Medical University and the Second Affiliated Hospital of Xuzhou Medical University. The physicians will ask eligible patients at a routine visit whether they would consider participating in the study. If the patient agrees to participate, declaration of informed consent is signed. A screening visit is carried out to ensure that the patients meet the criteria for participation.

Inclusion criteria consist of: (1) patients with CD needing a MRE examination and mid-gut tubing (prepared for FMT and/or enteral nutrition); and (2) aged ≥ 14 years. Exclusion criteria consist of: (1) being unable to understand or provide informed consent; (2) having difficulty in swallowing or dysphagia; (3) being allergic to laxative and/or contrast; (4) being claustrophobic or pregnant or with implanted metal objects or a cardiac pacemaker precluding performance of MRI; and (5) having a known or suspected intestinal obstruction or severe stricture.

### Randomization

Randomized sequences will be generated by the statistician from Department of Biostatistics, Nanjing Medical university. SAS 9.4 software will be used to generate a random sequence table for the participants. Ninety-six random numbers and the allocation sequence table of the randomized group will be kept as blind codes. The participants will be randomly divided into the oral group (n = 48) and tubing group (n = 48) at a ratio of 1:1. This sequence of randomization will be contained in opaque sealed envelopes and kept by the clinical research coordinator, who will be contacted competitively by each physician to provide the allocation. The principal physicians from the above three centers are responsible for enrolling patients.

### Oral group

Patients will be instructed to drink 2000 mL polyethylene glycol (PEG) solution over 60 min on the night before the MRE to remove stool and other impurities which may mimic lesions in the MRE. In addition, they will drink 1500 mL 3% mannitol solution gradually in the course of 60 min before MRE. An example of bowel preparation for MRE through oral administering is shown in Fig. 3a. If a patient fails to complete bowel preparation because of severe adverse symptoms such as nausea, vomiting, bloating, and abdominal pain and/or refusing to choose “oral” method, a tube will be placed in his or her mid-gut for MRE. Patients in the oral group will have a soft tube placed in the mid-gut after MRE for enteral nutrition or FMT.

**Fig. 3 Fig3:**
[figure not shown]
Methods of bowel preparation. Bowel preparation for MRE through oral administering (**a**) and mid-gut tubing (**b**)

### Tubing group

Patients will be inserted with a soft tube named mid-gut TET tube (8F, FMT-DT-N-27/1350, FMT Medical, Nanjing, China) in the mid-gut through endoscopy under anesthesia before the bowel preparation for MRE. If patients cannot tolerate endoscopy or anesthesia, a nasojejunal tube will be inserted under digital fluoroscopy. Patients will be instructed to take in 2000 mL PEG solution through the tube over 60 min on the night before MRE. In addition, 1500 mL 3% mannitol solution will be administered through the tube gradually in the course of 60 min before MRE to induce bowel distention. An example of bowel preparation for MRE through mid-gut tubing is shown in Fig. 3b. If a patient refuses the assigned mid-gut tubing before the MRE, or the tube falls off or blocks before the bowel preparation, the patient will be given the option of an alternative method.

All patients will have a colonoscopy examination within 24 h after the MRE. No change in the medical treatment will be made in this study until the colonoscopy examination is finished.

### MRE technique

All enrolled patients will be sent to the MRI department after bowel distention is induced. MRE examination will be performed using a 3.0-T clinical scanner (Signa HDxt, GE Healthcare) equipped with abdominal-pelvic coil (eight radiofrequency channels). Immediately before the scan, all patients will be given 20 mg of scopolamine-N-butyl bromide (Busco-pan; BoehringerIngelheim, Ingelheim, Germany) intravenously, to reduce bowel peristalsis motion artifacts. Patients will be scanned in the supine position. The MRE is carried out following the protocol [18, 19], including: (1) coronal T2 (single shot fast spin-echo [SSFSE]) through the abdomen and pelvis with breath-holding (Tck = 5 mm, spacing = 1 mm; TR = 2800 ms, TE = 70 ms); (2) axial T2 FSE fat-suppressed images covering the abdomen and pelvis, free-breathing with navigator triggering (Tck = 4 mm, spacing = 2 mm; TR = 12,000 ms, TE = 90 ms); and (3) axial T1 LAVA-Flex Mask through the abdomen and pelvis with breath-holding (Tck = 4 mm, spacing = 0 mm; TR = 4500 ms, TE = 1.7 ms). DW-MRI and DCE-MRI will be carried out after MRE. The whole imaging process takes approximately 45–50 min in total.

### Procedures

Over the one-week study period, the included patients will be instructed to answer a questionnaire about their mental pressure and discomfort (such as nausea, vomiting, bloating, abdominal pain, and diarrhea) before/during/after the bowel preparation for MRE. An overview of corresponding assessments is showed in Table 1. Two experienced radiologists will evaluate the grade of bowel distention. Two experienced endoscopists will evaluate the colonoscopy results.

**Table 1 Tab1:** Summary of measures to be collected

Variable				
Visit number/bowel preparation	0/Screening	1/Before	2/During	3/After
Day	~ − 3	− 1	0	1~3
Female-sex (%)	A	–	–	–
Age (years) (mean ± SD)	A	–	–	–
Height (mean ± SD)	A	–	–	–
Weight (mean ± SD)	A	–	–	–
Disease duration (years) (mean ± SD)	A	–	–	–
Disease location (n)	A	–	–	–
Small bowel disease	A	–	–	–
Small bowel + colonic disease	A	–	–	–
Upper GI	A	–	–	–
Perianal disease	A	–	–	–
Previous CD-related surgery (n)	A	–	–	–
HBI	A	–	–	–
Current medication (n)	A	–	–	–
Systematic corticosteroids	A	–	–	–
Thiopurines	A	–	–	–
Mesalazine	A	–	–	–
Anti-TNF	A	–	–	–
Mental pressure (median)	–	A	–	–
Degree of discomfort (median)	–			
Nausea	–	A	A	–
Vomiting	–	A	A	–
Bloating	–	A	A	
Abdominal pain	–	A	A	A
Diarrhea	–	–	–	A
Distention grade (median)				
Jejunum	–	–	A	–
Ileum, proximal	–	–	A	–
Ileum, distal	–	–	A	–
Colon (right part)	–	–	A	–
Colon (left part)	–	–	A	–
Preference to the method (n)	–	–	–	A
MRE lesion detection	–			
Terminal ileum	–	–	–	A
Ileocecal junction	–	–	–	A
Hepatic flexure of colon	–	–	–	A
Splenic flexure of colon	–	–	–	A
Rectosigmoid colon	–	–	–	A

*A* assessed, − not assessed, *SD* standard deviation, *GI* gastrointestinal, *CD* Crohn’s disease, *HBI* Harvey Bradshaw Index, *TNF* tumor necrosis factor

Mental pressure and degree of discomfort: using a visual 5-grade to describe (1 = few, 5 = very severe); distention grade of bowel segments: using a 5-grade scale (1 = 0–20% segmental distention, 2 = 20–40% distention, 3 = 40–60% distention, 4 = 60–80% distention, 5 = 80–100% distention); ileum, distal (the last 20–25 cm of terminal ileum). MRE lesion detection is evaluated by a 5-point scale (lesions locating at the terminal ileum, ileocecal junction, hepatic flexure of colon, splenic flexure of colon, and rectosigmoid colon, consistency of lesion detection from each bowel segment scoring 1 point, otherwise not scoring, confirmed by colonoscopy)

### Outcome measures

Table 1 lists the outcome measures and the time points at which they are collected during the study.

### The primary outcome

The primary outcome measures are: (1) degree of discomfort before/during/after bowel preparation for MRE using a visual 5-grade scale (1 = few, 5 = very severe). The bowel preparation includes two procedures, bowel cleaning and bowel distention, during which we use a visual 5-grade scale to describe the severity of nausea, vomiting, bloating, and abdominal pain (1 = few, 5 = very severe), respectively [20]. After the MRE, we use a visual 5-grade scale to describe the severity of abdominal pain and diarrhea. A lower score of adverse symptoms means a better compliance of the patient for bowel preparation for MRE; (2) grade of bowel distention evaluated by a 5-grade scale (1 = 0–20% segmental distention, 2 = 20–40% distention, 3 = 40–60% distention, 4 = 60–80% distention, 5 = 80–100% distention) [17, 21–23]. The distention grades of bowel segments, including jejunum, proximal ileum, distal ileum, right part colon, and left part colon, are assessed by two experienced radiologists, both of whom will be blinded to the information of allocation along above 5-grade scale. Different grades of bowel distention in the MR images achieved through two different methods are shown in the Fig. 4.

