### The secondary outcome

The secondary outcome measure is the accuracy of lesion detection through MRE confirmed by colonoscopy over a 5-point scale (lesions locating at the terminal ileum, ileocecal junction, hepatic flexure of colon, splenic flexure of colon, and rectosigmoid colon, consistency of lesion detection from each bowel segment scoring 1 point, otherwise not scoring). A higher score of distention grade of bowel segments and accuracy of lesion detection represents a better efficacy of bowel preparation for MRE.

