### Sample size calculation

The principal analysis will consist of the comparison between the proportions of bowel preparation that have reached physician–patient satisfaction score (degree of discomfort score ≤ 10, out of 50; grade of bowel distention score ≥ 20, out of 25; lesions detection point ≥ 4, out of 5) through mid-gut tubing and taking contrast compounds orally. Group sample sizes of 48 in the tubing group and 48 in the oral group achieve 80% power to detect a difference between the group proportions of 0.2500. The proportion in the tubing group is assumed to be 0.6000 under the null hypothesis and 0.8500 under the alternative hypothesis. The proportion in the oral group is 0.6000. The test statistic used is the two-sided Z test with unpooled variance. The significance level of the test was targeted at 0.0500. The significance level actually achieved by this design is 0.0506.

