### Statistical analysis plan

Considering the evaluation for grade of bowel distention, we will calculate the mean, standard deviation, and range of distention scores for each bowel segments and total segments between the two groups by using the Wilcoxon rank sum test. Similarly, we will use the same methods to analyze adverse symptom severity and the accuracy of lesion detection between the two groups. We will compare the proportion of bowel preparation for MRE reaching physician–patient satisfaction score between two groups by using the Chi-square test as our primary analysis. We will also explore the correlations between grade of bowel distention and severity of adverse symptoms by using Spearman’s correlation coefficient. The patients’ preference between the two methods for MRE will be compared using the signed-rank test. All statistical analysis will be done using SPSS software (version 19.0; SPSS Inc., Chicago, IL). *P* < 0.05 will be considered statistically significant.

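### The outcome section and the analysis section name different primary endpoints: discomfort and distention are declared, but a satisfaction composite is powered and called primary

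*Protocol article*

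**What the plan says.** The Abstract and the section on the primary outcome both declare two primary outcomes. The latter has "The primary outcome measures are: (1) degree of discomfort before/during/after bowel preparation for MRE using a visual 5-grade scale" and then "2) grade of bowel distention evaluated by a 5-grade scale". The next section gives the only secondary outcome: "The secondary outcome measure is the accuracy of lesion detection through MRE confirmed by colonoscopy over a 5-point scale".

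The section on sample size calculation takes a different endpoint: "The principal analysis will consist of the comparison between the proportions of bowel preparation that have reached physician–patient satisfaction score". The score is defined by thresholds on three quantities, the last of them scored on a five-point scale: "degree of discomfort score ≤ 10, out of 50; grade of bowel distention score ≥ 20, out of 25; lesions detection point ≥ 4, out". The 48 per group, the 80% power and the assumed rates of 0.60 and 0.85 all refer to this proportion.

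The section on the statistical analysis plan confirms that choice, comparing the proportion "reaching physician–patient satisfaction score between two groups by using the Chi-square test as our primary analysis". It also plans to compare "distention scores for each bowel segments and total segments between the two groups by using the Wilcoxon rank sum test", and to treat symptom severity and lesion accuracy in the same way. One threshold, P below 0.05, is set for all of these. No order of testing is given.

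The satisfaction score does not appear as an outcome in the Abstract, in either outcome section or in Table 1.

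**The concern.** A reader who starts from the outcome sections judges the trial on discomfort and distention. A reader who starts from the sample size and analysis sections judges it on the composite. The text supports both.

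The results could well diverge. The Discussion cites an earlier comparison in which tubing improved distention. It also says that the pilot experience on symptoms ran contrary to an earlier tubing study, probably because of infusion rate. Distention could therefore improve without discomfort doing so. The composite could also separate the arms through lesion detection, which is declared secondary. The trial is open-label and discomfort is patient-reported, so the headline result should not be left to be chosen once data are in.

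At stake are the false-positive rate of the claim that the trial is positive, and whether the endpoint that carries the claim was powered.

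**Working it through.** **1. Labels side by side**

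| Quantity | Abstract and outcome sections | Sample size and analysis sections |
|---|---|---|
| Discomfort | Primary | One part of the composite; also tested by Wilcoxon |
| Distention | Primary | One part of the composite; also tested by Wilcoxon |
| Lesion detection | Secondary | One part of the composite; also tested by Wilcoxon |
| Satisfaction composite | Not listed | Principal/primary analysis; the only one powered |

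**2. The stated sample size belongs to the composite**

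Inputs from the sample size section: 0.60 against 0.85, difference 0.25, two-sided 0.05, 80% power, unpooled Z test.

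- n = [0.60×0.40 + 0.85×0.15] × (1.960 + 0.842)² / 0.25² = 0.3675 × 7.849 / 0.0625 = 46.2, so 47 per group. The pooled formula gives 49.
- Power at 48 per group: 81.5% (unpooled approximation), 79.3% (pooled approximation), 81.6% (exact, unpooled Z), 80.4% (exact, uncorrected Chi-square).

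The plan's 48 per group at 80% is thus reproduced for the composite. For discomfort and distention the article gives no effect size or standard deviation, so no power can be computed.

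**3. False-positive chance if more than one result could be claimed as primary**

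Each test is at 0.05. Under independence the chance of at least one false positive is 1 − 0.95^m:

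- m = 2 (total discomfort, total distention): 1 − 0.95² = 9.75%.
- m = 3 (adding the composite): 1 − 0.95³ = 14.3%.

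The composite is built partly from the other two, so independence is not realistic. The documents give no correlations. The following are assumed values, with equally correlated normal test statistics and 1,000,000 simulated draws:

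| Assumed correlation | Two tests | Three tests |
|---|---|---|
| 0.3 | 9.5% | 13.6% |
| 0.5 | 9.1% | 12.5% |
| 0.8 | 7.8% | 9.8% |

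Whatever the dependence, the chance cannot exceed 2 × 0.05 = 10% for two tests or 3 × 0.05 = 15% for three.

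**4. Cost of the two ways out**

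- Composite as sole primary at 0.05: 48 per group stands, with 80–82% exact power on the stated rates.
- Sharing alpha by Bonferroni: the composite would need 56 (unpooled) to 60 (pooled) per group at 0.025, or 62 to 66 at 0.0167. At 48 per group its power would fall to 70–73% or 64–68%.

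**The case against.** The strongest reply is that the plan does name its decisive test. The sample size and analysis sections agree on the composite, no other test is called principal or primary, and only this one is powered. Two of its three parts are thresholds on the declared primary outcomes, and the Discussion explains the idea behind it. Test order and multiplicity rules are commonly left to a full analysis plan that is not shown.

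Much of this stands. A reader might infer that nothing in the article says which result decides the trial; the two sections just cited contradict that. A reader might also count every planned comparison (the composite, ten symptom items, five segments and two totals, 18 in all) and compute 1 − 0.95^18 = 60%. The documents do not support that figure. It treats totals as independent of the items that make them up, and nothing in the article says that a single symptom or segment could make the trial positive. A general 0.05 threshold sets a nominal level, not a rule for winning.

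The conflict of labels is not answered. An unseen analysis plan cannot settle it while the protocol declares one pair of primary outcomes and designates a different endpoint for its primary analysis.

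**Conclusion.** The point holds as a contradiction in the current text. The declared primary outcomes are not the endpoint that is powered and designated for the primary analysis, and that endpoint is unlisted and includes the secondary outcome.

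If any of the three could be presented as the primary result, the false-positive chance is 14.3% under independence and about 10–14% with correlation 0.3–0.8. For the two declared primaries alone it is 9.75%, or about 8–9.5%. These figures rest on the assumed correlations and on the primary-analysis label not being treated as binding. If the composite is held to be the sole primary endpoint, alpha stays at 0.05 and the stated sample size is adequate on the stated rates.

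**What to change.** By dated amendment before analysis:

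- List the satisfaction composite in the Abstract and in the section on the primary outcome as the single primary endpoint, at two-sided 0.05. Say explicitly that all three thresholds must be met; the sample size section implies this but does not state it.
- Make total discomfort and total distention secondary endpoints, claimed as confirmatory only if the composite is significant and in an order stated in advance.
- Treat individual symptoms and bowel segments as descriptive.
- Check the registry entry, which was not available here, and align it if it differs.

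No extra patients are needed on the stated rates. The cost is that a positive result on discomfort or distention alone can no longer be presented as a positive trial. It is also more than an edit of wording: the article reports 29 patients already included in an open-label trial, so the change needs a dated justification.

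The discomfort threshold is a separate problem. The outcome section implies ten items scored 1 to 5 (four symptoms in each of two procedures, plus two after MRE). The total then runs from 10 to 50, and a total of 10 or less requires the lowest grade on every item. If that threshold is changed, the assumed rates of 0.60 and 0.85, and with them the sample size, must be rechecked.
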